### **Randomization of Foot Selection and Order of Evaluation**

After enrollment, the prosthetic devices for each subject, as well as the order in which they will be evaluated, will be randomized using a computer generated algorithm that randomly selects from all available devices and then assigns the order. As determined by subject's weight, height and activity level (activity level rating is based on parameters set by the particular manufacturer/foot), each randomly selected foot will be purchased from the manufacturer by the study coordinator, under the supervision of the principal investigator, at the VANYHHS.

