### Specific Aim 2– To evaluate the kinematic and kinetic differences of non-articulating ESR, articulating ESR, and active plantar flexion ESR feet in individuals with transtibial amputation

Hypothesis 2.1 Plantarflexion forces (i.e. ground reaction forces) at push off /terminal stance will be most symmetrical to the intact limb for active plantarflexion devices, followed by non-articulating ESR feet, and lastly articulating ESR devices.

Hypothesis 2.2 Biomechanical symmetry in gait while negotiating a decline will be greater for both active plantarflexion ESR and articulating ankle ESR conditions compared to non-articulating ESR feet.

Hypothesis 2.3 Biomechanical symmetry in gait while negotiating an incline will be greatest for devices with active plantarflexion, followed by articulating devices, and lastly non-articulating ESR feet.

Hypothesis 2.4 Ambulation at a faster than self-selected walking speed will yield decreased symmetry in articulating ankle ESR and non-articulating ESR feet but not with the active plantar flexion ESR feet.

Hypothesis 2.5 Articulating ESR feet will not yield significant differences in gait symmetry regardless of specific foot assigned within the articulating ESR category.

**Specific Aim 3 – To correlate biomechanical findings with functional and subjective outcome measures and with user preference determined through activity monitoring and user satisfaction to develop guidelines for appropriate prosthetic prescription.**

Hypothesis 3.1 Individuals that commonly negotiate ramps, hills, inclines or declines will show preference for an articulating ankle ESR and/or active plantarflexion ESR feet over non-articulating ESR feet

Hypothesis 3.2 Individuals that have higher step counts, but do so at a low activity level will prefer the active plantarflexion ESR ankle-foot prosthesis.

Hypothesis 3.3 The majority of subjects will chose to utilize a single prosthesis for all activities, and not use different prostheses for different activities, as measured through step activity monitoring and daily activity logs.

Hypothesis 3.4 Step activity performance will, and age will not, correlate with prosthetic feet category that best optimizes function.

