### **Foot Selection:**

Prosthetic ankle-foot units included in this study will be grouped in to three categories: 1) Non-articulating ESR - this group will be any qualifying ESR ankle-foot unit that is commercially available. This will typically be the foot the subject is currently using. This group contains over 100 commercially available prosthetic feet, and will be randomly chosen from all available options that fit the subject’s anatomy if the user does not current have a non-articulating ESR foot. 2) Articulating ESR – this group includes all commercially available options

that have an articulating ankle and also have ESR qualities, currently Endolite Echelon, Fillauer Motion Foot, Freedom Innovations Kinterra, Endolite Elan, Ossur Propriofoot, Hosmer Raize, Otto Bock Triton Smart Ankle, and Ossur Proflex (Figure 2) meet this criteria. 3) Active (Powered) Plantarflexion - the third group will contain all commercially available ESR ankle-foot units with active plantarflexion. Currently, the iWalk BiOM is the only foot that would be classified into the Active Plantarflexion ESR group. If new prosthetic feet-ankle units become commercially available during the course of this study, they will be added to the appropriate groups.

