## **Specific Aim 2:**

Specific Aim 2 will be addressed through a subset of  $n=30$  subjects which will undergo kinematic and kinetic biomechanical evaluations at the completion of each acclimation period for Parts 2-4. This will include kinetic and kinematic evaluation on level ground walking, and additional kinematic evaluation on inclines and declines.

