#### Power Analysis:

| Site                                                | n   | n for subset |
|-----------------------------------------------------|------------|---------------------|
| VA New York Harbor Healthcare System (NYC)          | 30         | 15                  |
| Walter Reed National Military Medical Center (D.C.) | 30         | 15                  |
| VA Puget Sound Healthcare System (Seattle)          | 30         | 0                   |
| James J. Peters VA Medical Center (Tampa)           | 30         | 0                   |
| TOTAL                                        | 120 | 30           |

Figure 7. Total Subjects per site to be seen over the course of 3 year period

#### Specific Aim 1

Functional measures will be analyzed by multilevel (site) repeated measures analysis of variance. Because order of prosthesis will be randomized, there should be no order effect. However, order will be included in the initial analysis to test this assumption. Assuming an alpha error rate of 5% and within-group standard deviation of 5, 120 subjects will provide over 98% power to detect a 3 unit difference between at least two of the ESR groups for each of the functional measures.

### Specific Aim 2

Kinematic and kinetic measures will be analyzed by multilevel (site) repeated measures analysis of variance. Because order of prosthesis will be randomized, there should be no order effect. However, order will be included in the initial analysis to test this assumption. Assuming an alpha error rate of 5% and within-group standard deviation of 10, 30 subjects will provide 72% power to detect a 6-unit difference between at least two of the ESR groups for each of the measures.

### Specific Aim 3

This analysis will be performed using paired t-test to determine correlations between prosthesis chosen as per SAM data and which functional outcome measures are indicative of that choice. Additionally pair t-test will be performed between kinematic and kinetic data to again correlate with the prosthetic choice of the subject as demonstrated through the SAM data. Finally all SAM data will be evaluated against the activity journal to determine the roll of a specific activity goal and a specific prosthesis.

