## **Data Management**

### **A. Data Management**

#### **Data Management between sites:**

##### *Data Management Between Sites:*

A one-day training kick off meeting will be held at the VA NYHHS prior to study initiation to review and train research staff on the research protocol for each site. This will include comprehensive training of each aspect of the protocol, including fittings, device trainings, data collection and recording, data analysis, and sharing of results.

An additional training will take place between the NYHHS and WRNMMC to review the biomechanical gait analysis between sites. While an interlab reliability and validity study has not been conducted between WRNMMC and VA NYHHS at this time, a proposal to conduct this study has been developed and preliminary funding has been identified. We plan to conduct this investigation prior study initiation and expect positive findings by implementing the recommendations provided in the military treatment facility interlab reliability study (Data was presented at Gait and Clinical Movement Analysis Society 2015 Meeting, March 18-21, Portland, OR). We plan to use identical marker sets and analysis, including identical anatomical segment definitions, to reduce variability between the labs to ensure consistent data collection and analysis.

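### The specific articulating foot is drawn with no stated balance by site or gait subset, so some feet will probably be missing from a gait lab or have almost no wearers, which limits coverage and precision for Hypothesis 2.5

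*Protocol*

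**What the plan says.** The section Randomization of Foot Selection and Order of Evaluation states that devices and their order are "randomized using a computer generated algorithm that randomly selects from all available devices and then assigns the order". The only limits it gives are those of fit: "As determined by subject's weight, height and activity level". It mentions no stratum, block or quota by site, lab or gait subset.

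The draw of a specific foot matters mainly in the articulating category. Under Foot Selection, the non-articulating foot will usually be the one the subject already wears, and the powered category currently holds a single device. The articulating category holds eight: "currently Endolite Echelon, Fillauer Motion Foot, Freedom Innovations Kinterra, Endolite Elan, Ossur Propriofoot, Hosmer Raize, Otto Bock Triton Smart Ankle, and Ossur Proflex". The pool may grow: "If new prosthetic feet-ankle units become commercially available during the course of this study, they will be added to the appropriate groups".

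The specific foot is itself a research question. Hypothesis 2.5 reads "Articulating ESR feet will not yield significant differences in gait symmetry regardless of specific foot assigned within the articulating ESR category". Hypothesis 1.5 asks the same of functional outcomes. The justification for including all feet promises an internal analysis to test the groupings and look for outliers.

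Gait data come only from a subset of 30 who "undergo kinematic and kinetic biomechanical evaluations at the completion of each acclimation period for Parts 2-4". The table under Power Analysis places 15 of them at New York and 15 at Walter Reed. On the two labs, Data Management says "While an interlab reliability and validity study has not been conducted between WRNMMC and VA NYHHS at this time". It adds that such a study is planned before the trial starts and that marker sets and analysis will be identical.

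**The concern.** Thirty subjects over eight feet is 3.75 per foot, or 15/8 = 1.9 per foot and lab. At that size a purely random draw produces empty cells as a matter of course. A foot with no wearer in the subset drops out of Hypothesis 2.5. A foot with one wearer cannot be told apart from that subject. A foot seen in one lab only gives no way to check whether its result holds in the other lab. An outlying foot, which the protocol says it wants to detect, may be the one with no data. The allocation is fixed at enrolment, so no later analysis can restore the lost coverage, although the same 30 subjects could be spread almost evenly.

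**Working it through.** **Inputs.** 8 articulating feet (Foot Selection); 15 gait subjects in each of 2 labs, 4 sites of 30 (Power Analysis); SD 10 for Aim 2 measures (Power Analysis). Assumption: independent draws with probability 1/8 per foot. The protocol does not state the probabilities, so a range is given below.

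**The plan's own figure.** The 72% power for Aim 2 concerns the three foot categories, not specific feet. A repeated-measures F test, with one category midway between two that differ by 6 units, gives 71.8% at a within-subject correlation of 0.36. The protocol does not state that correlation, so the figure can be neither confirmed nor faulted. Nothing here rests on it.

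**A given foot.**
- Absent from one lab: (7/8)^15 = 0.135.
- Absent from at least one of the two labs: 2 × 0.875^15 − 0.875^30 = 0.270 − 0.018 = 0.252. Over 8 feet, about 2.0 are expected.
- At most one wearer of 30: 0.875^30 + 30 × (1/8) × 0.875^29 = 0.018 + 0.078 = 0.096.

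**Any of the eight feet.**
- Some foot absent from a given lab, by inclusion–exclusion: 8(0.875)^15 − 28(0.75)^15 + 56(0.625)^15 − 70(0.5)^15 + … = 0.752. For at least one of the two labs: 1 − (1 − 0.752)² = 0.938.
- Some foot with no wearer among the 30: 8(0.875)^30 − 28(0.75)^30 + … = 0.141.
- Some foot with at most one wearer: 0.607, confirmed by simulation.

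**Range.**

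| Pool | Some foot absent from a lab | Some foot with at most 1 wearer |
|---|---|---|
| 6 feet | 58% | 17% |
| 7 feet | 81% | 37% |
| 8 feet, equal | 94% | 61% |
| 8 feet, probabilities from 0.5 to 1.5 times 1/8 | 98% | 84% |
| 9 feet | 98.6% | 81% |
| 10 feet | 99.8% | 93% |

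Unequal eligibility or a larger pool makes it worse. Only a smaller pool helps.

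**Precision.** Averaged over simulated allocations, the lab-adjusted variance of a foot-versus-foot contrast is 0.72–0.74 σ² with the unrestricted draw. With permuted blocks of 8 within each lab it is 0.54–0.55 σ². As a check, a perfectly even split would give 2/3.75 = 0.53 σ². The reduction is about 25% (0.73 to 0.55: 0.18/0.73). In the full sample some foot is absent from some site with probability 1 − (1 − 0.141)^4 = 0.455, and blocking lowers the variance by only about 8%.

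**Counts under blocking.** Each lab's 15 subjects are one full block of 8 plus 7 of the next, so every foot appears once or twice per lab. Totals are 3 or 4, except that the foot left out of the second block may be the same in both labs (probability 1/8), which gives a total of 2. No foot is missing from a lab while the pool is fixed and every foot fits.

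**Power for Hypothesis 2.5.** Take two feet 6 units apart, one 3 above and one 3 below the rest. With SD 10 applied to subject-level values, the noncentrality is 3.75 × (3² + 3²)/10² = 0.675 on 7 and 21 degrees of freedom. Power averages 6.8% unrestricted and 6.9% blocked. For one foot 20 units away from the others it is about 54% and 59%.

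**The case against.** A reader might infer that a foot tested in one lab only cannot be separated from that lab, so that Hypothesis 2.5 is confounded. The documents do not support that.
- Power Analysis already specifies a multilevel analysis with site. In an additive model the lab effect is estimated from feet worn in both labs. In 3,000 simulated unrestricted draws, the foot-plus-lab model was of full rank for every foot worn at least once. Adjusting for lab raised the mean contrast variance only from 0.69 to 0.72 σ².
- Each subject is measured in one lab under all three categories, and symmetry compares limbs within that lab. A constant offset between labs therefore largely cancels.
- The inter-lab reliability study is planned before the trial starts.

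What remains is narrower: for a foot seen in one lab only, a foot-by-lab interaction cannot be checked.

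It can also be said that the protocol does not call the draw simple or unblocked, and that a separate randomisation specification may add restrictions. That is fair, and the figures depend on it. The protocol does, however, describe the draw and its limits and names no balancing factor. Ordinary blocking would not be enough either: blocks of 8 run over exactly these 30 subjects without regard to lab still leave a foot missing from a lab in about 66% of draws, though none with at most one wearer.

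Finally, restriction hardly moves the overall power for Hypothesis 2.5. That stands: the limit there is 3.75 subjects per foot. Fit limits and new devices will also make the balance approximate, but in simulation nearly all the benefit remained when subjects were ineligible at random for 20–40% of feet.

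**Conclusion.** The point holds as a cheap improvement in coverage and precision. On equal, independent draws of eight feet, the stated method leaves some foot out of a lab in about 94% of allocations, with at most one wearer in about 61% and with none in about 14%. Balanced lists remove most of this and lower the mean foot-contrast variance in the gait subset by about a quarter.

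It should not be read as more than that. The imbalance arises by chance and does not bias the foot comparisons. Comparisons between the three categories are not affected, because every subject wears one foot from each. Balancing does not rescue Hypothesis 2.5, which stays at about 7% power for a 6-unit difference between two feet. For Hypothesis 1.5, with 120/8 = 15 subjects per foot, the gain is modest.

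**What to change.** State in the randomisation section that:
- the articulating foot is drawn from permuted lists of the available feet within each site, with a separate list for gait-subset subjects at New York and Walter Reed, since only 15 of the 30 subjects at each belong to the subset;
- if the drawn foot does not fit under the existing criteria, the next eligible foot on the list is taken, and the skipped foot is carried forward to the next eligible subject and recorded;
- a device that joins the pool is added to the subsequent blocks;
- the order of the three categories is still randomised.

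Subset membership has to be known before the foot is drawn. The cost is a somewhat more complex randomisation program, with no extra subjects or visits. Balance will be only approximate when eligibility varies or devices are added. Predictability of the list matters little, because every subject receives all three categories. The protocol should also say that comparisons between specific feet in the gait subset remain imprecise even with balanced counts.

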### **Exclusion criteria:**

- subjects with active wounds/ulcers or significant musculoskeletal comorbidities on their intact limb that would impair their ability to participate in all functional outcome measures
- subjects with knee flexion contracture > 5 degrees
- any comorbidity that results in rapid limb volume changes (i.e. end stage renal disease with dialysis),
- a poorly fitting socket
- cognitive deficit(s) or mental health pathology limiting a subject’s ability to participate fully in the study
- subjects who are unable or unwilling to comply with all research visits
- women who are pregnant or who plan to become pregnant in the near future
- subject weighs more than product weight load maximums
- score of less than “modified independence” on any of the FIM mobility items

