The PEQ contains a VAS for pain within the evaluation. Spearman correlations, a statistical measure of the strength of a monotonic relationship between paired data will be calculated to correlate data between pain and functional outcome values across the 3 groups. Linear mixed-effects models will be used to identify statistically significant differences in pain scores and functional outcome variables. In the case of significance, pair-wise comparisons will be tested for significance using linear contrasts with Tukey's Honestly Significant Difference or applying Bonferroni's correction. Finally, stepwise multiple regression will be performed with VAS pain as the dependent variable. The independent variables will be comprised of functional parameters and condition (foot type). Significance will be set at  $p < 0.05$ . Variables will be eliminated if  $p$  is  $> 0.1$ .

*Hypothesis 1.4 There will be no significant differences in functional outcome measures within all tested non-articulating ESR feet regardless of specific foot assigned.*

*Hypothesis 1.5 There will be no significant differences in functional outcomes within all articulating ESR feet tested regardless of specific foot assigned.*

Functional measures will be analyzed by multilevel (site) repeated measures analysis of variance. Because order of prosthesis will be randomized, there should be no order effect. However, order will be included in the initial analysis to test this assumption. When the ANOVA reveals significant differences ( $p < 0.05$ ), we will apply pairwise comparisons using related pairs t-tests to identify the source of differences ( $p < 0.05$ ).

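### Hypotheses 1.5 and 2.5 compare articulating models between different subjects, yet the draw is not described as balanced, models can join mid-study, and the text leaves open whether subject traits restrict the draw

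*Protocol*

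**What the plan says.** **The draw.** Under Randomization of Foot Selection and Order of Evaluation, devices and their order are "randomized using a computer generated algorithm that randomly selects from all available devices and then assigns the order". The next sentence names the subject's weight, height and activity level and continues: "activity level rating is based on parameters set by the particular manufacturer/foot), each randomly selected foot will be purchased from the manufacturer". No balancing across models is described.

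**The pool.** Foot Selection names eight articulating models and adds: "If new prosthetic feet-ankle units become commercially available during the course of this study, they will be added to the appropriate groups". For the non-articulating category only, and only for subjects who have no such foot already, the draw is limited by fit: the foot "will be randomly chosen from all available options that fit the subject’s anatomy". The exclusion criteria remove a subject if the "subject weighs more than product weight load maximums".

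**The hypotheses.** "Hypothesis 1.5 There will be no significant differences in functional outcomes within all articulating ESR feet tested regardless of specific foot assigned". Hypothesis 2.5, under Specific Aim 2, says the same of gait symmetry.

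**The analysis.** For Hypotheses 1.4 and 1.5 the plan gives a multilevel (site) repeated-measures analysis of variance that tests order, followed by related-pairs t-tests. SA2 Statistical Analysis uses foot condition as the predictor and has no term for individual models. The justification for including all commercial feet promises a within-group analysis to confirm or overturn the groupings, without a method.

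**The concern.** There are three categories and three prostheses per subject, so each subject contributes one articulating model. Any contrast between models is then a contrast between groups of people, and its validity depends on how models are allocated. Three features weaken that allocation.

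- With plain random selection the counts per model will be uneven, and some models may hardly be tested in the gait subset.
- A model added during the study can go only to later enrollees, so it should not be compared with subjects who could not have received it.
- If weight, height or activity level decides which models a subject may draw, the groups differ in traits that plausibly bear on walking performance. A model could then look better only because more active subjects were eligible for it.

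The answer decides whether the articulating category stands as one group, and the prescription criteria are built on these categories. A later analysis plan can add covariates, but it cannot recover eligibility sets that were never stored or rebalance counts after the draw.

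**Working it through.** **1. The plan's own figure.** No power is stated for Hypothesis 1.5 or 2.5. The nearest figure is Aim 1: SD 5, 120 subjects, 3 units between at least two of three categories, over 98% power. With means −1.5, 0, +1.5 and zero within-subject correlation, λ = 120 × (1.5² + 0 + 1.5²) / 5² = 21.6. On 2 and 238 degrees of freedom the power is 99.0%, so the figure is reproduced. It applies to categories in which every subject is seen three times.

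**2. Subjects per model.** One articulating foot each, eight models: 120/8 = 15 for Hypothesis 1.5 and 30/8 = 3.75 for Hypothesis 2.5. The noncentrality for one pair of models is difference / (SD × √(2/n)):

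- Aim 1 inputs: 3 / (5 × √(2/15)) = 1.64, power about 35%.
- Aim 2 inputs (6 units, SD 10): 6 / (10 × √(2/3.75)) = 0.82, power about 10%.

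**3. Balance.** Assume eight models, each equally likely and drawn independently.

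- Some model unused among 30 subjects: 8(7/8)³⁰ − 28(6/8)³⁰ + … = 0.1457 − 0.0050 + … = 14%.
- Some model with 0 or 1 subject: 1 − (30!/8³⁰) × [coefficient of x³⁰ in (eˣ − 1 − x)⁸] = 61%.
- A balanced draw gives 3 or 4 each.
- At 120 subjects, the median smallest model has 10 subjects and the median largest 20.

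**4. Confounding, if the traits restrict the draw.** All inputs here are assumptions, because the documents give none. There is no true model difference. Two, three or four of eight models are open only to the more active subjects, and being in that group shifts the outcome by 0.5 or 1 SD. The test is a one-way F-test at 5% on the articulating-foot outcome.

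| Subjects | Restricted models open to | Shift | False-positive rate (2 / 3 / 4 models) |
|---|---|---|---|
| 120 | 50% | 0.5 SD | 9 / 12 / 15% |
| 120 | 50% | 1 SD | 19 / 31 / 48% |
| 120 | 90% | 0.5–1 SD | about 5–8% |
| 30 | 50% | 0.5–1 SD | about 6–11% |

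Repeat runs agree within about one percentage point; the most extreme 90% setting gave 9% in one repeat. With the trait in the model, the rate at 120 subjects is 5–6%.

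A second set-up used a continuous trait correlated 0.2–0.6 with the outcome and restricted models open to 50–90% of subjects. It gave about 5–55% at 120 subjects and 4–11% at 30, with spurious gaps of 0.2–3.2 units at SD 5. Adjusting for the trait, or analysing change from another foot worn by the same subject, brought the rate back to about 4–6%.

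**5. The follow-up test.** Related-pairs t-tests need both members of a pair in one subject. Two articulating models are never worn by the same subject, so these tests cannot locate a difference between models.

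**The case against.** A reader might infer that the model a subject receives is fixed by weight, height and activity level, and that the model comparisons are therefore confounded. The documents do not establish this. The algorithm "randomly selects from all available devices and then assigns the order", and the traits are mentioned only when the already selected foot is bought. A rating on the particular foot's own parameters suggests that the foot is known by then. A fit filter is written only for non-articulating feet, and excluding subjects above product weight limits reduces any dependence on weight. Specifying size or stiffness is thus a natural reading. This stands, and it is why the confounding part is conditional.

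The high error rates also need restricted models to be closed to half the subjects. Entry is already limited to independent walkers, and at 90% eligibility the inflation is small. In the gait subset it is small in most settings, and nothing in the documents links activity to symmetry. This stands too.

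The simulated one-way test is not the planned repeated-measures model. If a subject's other feet serve as reference, stable additive traits cancel. That is correct, but the plan does not specify this contrast for models. Additivity is not assured either: Hypothesis 3.2 expects activity pattern to bear on which category is preferred.

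Uneven counts cost precision and create no bias, and covariate lists are commonly left to the analysis plan. Both are true. Balancing would not rescue Hypothesis 2.5 either, at about 10% power per pair. What remains is the ambiguity in the draw, the time dependence of later-added models, and counts that a better draw would even out at almost no cost.

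**Conclusion.** The point holds as a recommended design improvement, in two parts.

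**Independent of the ambiguity.** Models are compared between subjects under a draw with no balancing described. With 30 subjects over eight equally likely models, some model has 0 or 1 subject in 61% of draws and none in 14%. Any model added later is tied to enrolment period. The time element matters only if new models do appear.

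**Conditional.** If the traits restrict the draw, differences between models partly reflect who could receive them. The documents do not fix the size. On the assumptions above, the false-positive rate at 120 subjects runs from about 5–8% (90% eligibility) to 48% (half eligible, four models, 1 SD shift), and at 30 subjects is about 5–11%. If the traits only specify the version ordered, there is no such bias.

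It would go too far to say that the plan commits to an unadjusted comparison. For Hypothesis 1.5 it names site and order, and for Hypothesis 2.5 it writes no model-level analysis at all.

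**What to change.** 1. State in the randomization section whether weight, height and activity level restrict which model can be drawn. If they do, store each subject's eligible models at the time of the draw.
2. Have the central program favour, with high probability, the least-used eligible articulating model, separately for the gait subset.
3. For Hypotheses 1.5 and 2.5, adjust for weight, height and one activity measure common to all models and recorded before the draw. The manufacturer's rating will not serve, because its scale differs between models. Part 5 step counts come after the feet are issued. Alternatively, analyse each subject's change from the other feet worn, and replace the related-pairs tests with between-subject contrasts of models.
4. Compare a later-added model only with concurrently enrolled subjects.
5. Treat Hypothesis 2.5 as descriptive and keep covariates few: 30 subjects less 8 models leaves 22 residual degrees of freedom, and four covariates would leave 18.

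**Cost.** A small change to the selection program, one stored list and one baseline activity item (Part 1a already collects height and weight), and a few degrees of freedom. The change score has its own price. With within-subject correlation ρ its SD is SD × √(2(1 − ρ)), so it is less variable than the raw score only when ρ exceeds 0.5.
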